### Sample size

2.3.

The sample size was computed using the GRANMO sample size calculator. We considered the estimation of the relative risk (RR) for a cohort study (using the Poisson approximation), with 10 years of follow-up and a rate of loss to follow-up of 30%, accepting an alpha risk of 0.05 and a beta risk of 0.2 in a bilateral contrast. The incidence of morbidity was considered as the main dependent variable and was around 60% in a previous analysis with 10.14 years follow-up (2). Health literacy was considered as the main independent variable. According to the questionnaire HLS-EU, 58,3% of the Spanish population has an inadequate or problematic level of health literacy (47). Low levels of health literacy have been linked to poorer physical and mental health outcomes, increased use of health services (68–70), and higher all-cause mortality (71, 72). Taking all these parameters into account, a sample of 3,083 persons is required, 1,793 in the exposed group (inadequate or problematic health literacy, HLS-EU-Q16 score between 0 and 12) and 1,290 in the non-exposed group (HLS-EU-Q16 score between 13 and 16). The sample size has been calculated to detect a minimum RR of 1.1 at 10 years, and will allow the detection of a minimum RR of 1.2 at 5 years, which is lower than some of the figures reported in the literature (73).

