The dependent variables in this study are morbidity, all-cause mortality, adoption of healthy lifestyles, quality of life, and utilization of health services. The information regarding the main dependent variables will be recorded at baseline and during the follow-ups at 5 and 10 years through surveys, physical examination and review of the medical records. The presence of morbidities will be assessed through the diagnoses in the medical records and physical examination. The medical records will also be the source to assess all-cause mortality.

Regarding the physical examination, blood pressure of participants will be measured and hypertension defined following the recommendations and criteria of the Spanish Hypertension Society. The ankle-brachial index (ABI) will be measured with a Vasera device (Fukuda Denshi), and peripheral arterial disease considered when ABI < 0.9. Weight and height will be measured to obtain the body mass index (BMI), and overweight and obesity will be considered if 25 ≤ BMI < 30 and BMI > 30, respectively. Waist circumference will also be measured. Blood testing will be performed to measure fasting glucose levels, glycated hemoglobin (HbA1c), total, low and high-density lipoprotein cholesterol, triglycerides, and creatinine.

For each participant, morbidity will be recorded at baseline and during follow-up by considering all the active conditions in the medical records at the time of the visit. We will define incident morbidity as the onset of any of the following 17 group conditions, provided they are not present at baseline: hypertension, ischemic heart disease (angina or acute myocardial infarction), heart failure, cardiac arrhythmias, diabetes mellitus, ischemic stroke, peripheral arterial disease, chronic obstructive pulmonary disease, asthma, any type of arthritis, osteoporosis, any type of cancer, Parkinson’s disease, one or more affective disorders (depression, anxiety), one or more psychotic disorders (schizophrenia, psychosis, bipolar disorder), dementia (including Alzheimer’s disease), and obesity. If we detect any frequent condition at follow-up that has not already been included in these 17 proposed groups, we will add a new group category.

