### Data collection process

2.5.

Once the project has been approved by the pertinent ethics committees, informative meetings will be held at the PHC centers to explain the project to health professionals so they can address any questions that may arise. Subsequently, assigned personnel (may vary according to the AACC) will be asked to prepare a list with the people ascribed to the PHC center who meet the inclusion criteria of the study and make a random selection of the necessary sample, oversampling by 30%, in order to be able to substitute participants that should be excluded. In some PHC centers, professionals will directly call possible participants to invite them to be included in the study. In other centers, permission will be requested from the professionals so that a person linked to the study makes the calls on their behalf in a centralized manner.

Participants recruitment: a letter will be sent by mail to the candidates with the study information sheet and 10 self-administered questionnaires: (1) the self-efficacy scale; (2) the resilience scale; (3) level of physical activity; (4) quality of life; (5) the sleep quality index; (6) a disability assessment; (7) occupational stress; (8) stressful life events; (9) the functional social support questionnaire; and (10) the SOGI questions. This letter will be sent to participants before or after the phone contact, as decided by each AACC. The person in charge of calling the participants will invite them to participate in the study and schedule a day and time to attend their PHC centers. If they accept, they will be asked to fill out the self-administered questionnaires and deliver them to a nurse at the PHC.

During the face-to-face visit, the person will be invited to sign the informed consent and clarify doubts, if any, about the information sheet and the study in general. In a confidential sheet, separate from the rest of the variables, the name, surnames, postal address, and contact telephone numbers will be recorded. A case identification number will be given. Study data will be collected and managed using REDCap (93, 94) electronic data capture tools hosted at *Fundació Institut Universitari per a la recerca a l’Atenció Primària de Salut Jordi Gol i Gurina* (IDIAPJGol).

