### Statistical analysis

2.6.

The statistical analysis will include a descriptive analysis. Percentages of the categorical variables will be calculated for each AACC. Continuous variables with a normal distribution will be described with the mean (standard deviation, SD); otherwise, the median (first and third quartile) will be used. The analyses will be stratified by sex. Bivariate analyses will be performed using the *t*-test for independent samples, or the Mann–Whitney test when required, to analyze continuous variables; and the Chi-squared test for proportions.

Objective one will analyze the incidence of morbidity, defined as the onset of any new condition out of the 17 considered. To this end, a Cox model will be built for each independent variable, and adjusted for the above-mentioned covariates. Potential heterogeneity between AACC will be estimated by introducing random effects in the model. Sensitivity analyses will examine loss to follow-up rates. Objective two will analyze the incidence of the rest of the dependent variables (except incidence of morbidity) using also Cox models, one for each of the six independent variables, adjusted for the covariates. We will calculate the incidence of all-cause mortality and its Kaplan–Meier, stratified by the categorical variables and AACC. Potential heterogeneity will be estimated, and sensitivity analyses performed as in objective one.

Before obtaining the follow-up information at 5 and 10 years, we will describe and analyze the gathered data at baseline. To this end, general linear multilevel models will be used to examine the association of the dependent variables (lifestyles, quality of life, and use of services), with the six independent variables, adjusted for the registered covariates (age, sex, occupational social class, social capital, functional capacity, and stress level). Potential disparities between AACC will be captured by including random effects in the models.

Statistical significance will be considered at *p*-values < 0.05. The analyses will be carried out using the Statistical Package for the Social Sciences (SPSS) version 26.0, and the R-software.

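### The models carry random effects for the nine regions only, although people are sampled within PHC centres, so standard errors may be understated where aptitudes and outcomes both cluster by centre

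*Protocol article*

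**What the plan says.** The design has three levels: people, PHC centres and nine AACC (protocol article, Aim, design and study setting; Participants). Under Data collection process, assigned personnel are to "prepare a list with the people ascribed to the PHC center who meet the inclusion criteria of the study and make a random selection". In some centres the local professionals make the recruitment call; in others a person linked to the study calls centrally.

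On the outcome, the Variables section states: "The presence of morbidities will be assessed through the diagnoses in the medical records and physical examination". Blood pressure, ankle-brachial index and body mass index are measured by the study.

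The Statistical analysis section sets one Cox model per aptitude and adds: "Potential heterogeneity between AACC will be estimated by introducing random effects in the model". The same handling is carried to objective two. The multilevel models for the baseline data also name AACC random effects, and so does the Methods part of the Abstract. No centre-level term and no cluster-robust variance is mentioned.

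The Sample size section plans for RR 1.1, "accepting an alpha risk of 0.05 and a beta risk of 0.2 in a bilateral contrast", and arrives at "a sample of 3,083 persons is required, 1,793 in the exposed group". It mentions no design effect.

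**The concern.** The unit from which people are drawn is missing from the models as described. People at the same centre may resemble each other in health literacy and the other aptitudes. They may share the staff who administer the questionnaires that Table 1 does not offer for self-completion, health literacy among them. Local practice in recording diagnoses may also be common to them. If exposure and outcome both cluster in this way, a model with region effects only counts correlated people as independent. Its intervals are then too narrow and its tests reject too often.

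The planned effect is small and the planned power is 80%, so there is little slack to absorb a larger standard error.

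**Working it through.** **1. Reproduce the planned sample size.** Inputs from the Sample size section: two-sided alpha 0.05, power 0.80, 30% loss, incidence about 60% (taken here as the risk in the non-exposed), RR 1.1 (hence 66% in the exposed), and 1,793 to 1,290, a ratio of 1.39.

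Log-RR formula for independent individuals:
- n0 = (1.960 + 0.842)² × [0.40/0.60 + 0.34/(0.66 × 1.39)] / (ln 1.1)² = 896.2
- Non-exposed with loss: 896.2/0.70 → 1,281
- Exposed with loss: 1.39 × 896.2/0.70 → 1,780
- Total: 3,061

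A comparison of two proportions with continuity correction gives 1,286 + 1,788 = 3,074. Both are within 1% of 3,083. (A pure Poisson variance would give about 8,000 and does not reproduce it.) Neither matching formula contains a design effect. With 70% retained, power for 60% against 66% is 81%.

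**2. Choose the right inflation.** The aptitudes are scores of individuals, so the familiar 1 + (m − 1) × ICC does not apply. For an individual-level exposure the variance inflation is about

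1 + (m − 1) × ICCx × ICCy,

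where m is the number of people per centre. The ICCs are those left within region after covariate adjustment. If either ICC is zero, the inflation is 1.

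**3. Put numbers in.** The number of centres and both ICCs are assumptions. The simulation had 3,083 people in nine regions, 1,500 replicates per setting, and a linear model with region effects only as a stand-in for the Cox model with a region random effect. The table gives true SE divided by model SE, with the type I error at nominal 0.05 in brackets.

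| ICCx / ICCy | 27 centres (m ≈ 114) | 54 centres (m ≈ 57) | 90 centres (m ≈ 34) |
|---|---|---|---|
| 0 / 0.05 | 1.01 (0.053) | 1.00 (0.052) | 0.99 (0.050) |
| 0.02 / 0.02 | 1.01 (0.053) | 1.02 (0.059) | 0.99 (0.055) |
| 0.05 / 0.05 | 1.10 (0.071) | 1.06 (0.065) | 1.02 (0.065) |
| 0.10 / 0.10 | 1.37 (0.153) | 1.25 (0.129) | 1.16 (0.088) |

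Simulation error in a ratio is about 1/√(2 × 1,500) = 0.018, so the first two rows cannot be told apart from no effect. The formula in step 2 agrees: for 54 centres at 0.05/0.05 it gives √(1 + 56 × 0.0025) = 1.07, against 1.06 simulated. With one centre per region (9 centres), the ratio stayed between 0.97 and 1.04 in all settings, because the region effect is then the centre effect.

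**4. Consequence for size and power.** The N needed to hold power is 3,083 × ratio².
- ICCs of 0.05: 3,083 × 1.019² ≈ 3,200 to 3,083 × 1.099² ≈ 3,720. Power falls from 81% to between 80% and 74%.
- ICCs of 0.10: 3,083 × 1.160² ≈ 4,150 to 3,083 × 1.372² ≈ 5,800. Power falls to between 69% and 55%.

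Power here is Φ(2.853/ratio − 1.960), where 2.853 = 1.960 + 0.893 corresponds to the starting 81%.

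**The case against.** The strongest reply is that nothing shows the standard errors to be wrong. The inflation depends on the product of two residual ICCs, and the documents give neither. Much of what makes neighbours alike is measured: occupational social class (from education and occupation), income, housing, and social capital including views of the local area. Adjustment for such covariates may leave little centre clustering. Several procedural differences, such as the timing of the letter, are decided by each AACC, which is the level modelled. Staff training and data quality control are planned. All of this stands, and it is why the effect may be negligible.

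A reader might infer that the standard errors certainly are too small, or might apply the cluster-exposure design effect and get a far larger figure. The documents support neither. Nor do they say that diagnoses are made or coded centre by centre. Medical records are not restricted to primary care, and the study examination bears directly on hypertension, peripheral arterial disease and obesity among the 17 condition groups.

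It can also be said that a condensed article leaves the full random-effects structure to an analysis plan that is not shown. This carries less weight. The article does state the level of the random effects, each time as the AACC, and that level is not the one at which people are sampled.

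**Conclusion.** The point holds as a conditional one. The models as described omit the centre, and the sample size makes no allowance for it. Standard errors may be understated for those aptitudes and outcomes that both cluster by centre within region after adjustment. For 27 to 90 centres and equal ICCs, the true standard error is larger than the model's by about 0–2% (ICCs 0.02), 2–10% (0.05) or 16–37% (0.10). It is not understated if the exposure does not cluster or there is one centre per region. These figures rest on assumed centre numbers and ICCs and on a linear stand-in for the Cox model; the documents cannot narrow the range. The change is worth making because it costs almost nothing if centre variance is near zero and protects the inference if it is not.

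**What to change.** In Statistical analysis (2.6), add a random intercept (frailty) for PHC centre nested within AACC to all Cox models and to the baseline multilevel models, keeping AACC as the upper level. State the fallback in advance: if a model does not converge, stratify by AACC and use robust standard errors clustered on centre. Record the centre for every participant, and report the number of centres and the estimated centre variance.

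This corrects the standard errors. It removes confounding by between-centre differences in recording only in part, and the fallback does not address that at all. As a sensitivity analysis, therefore, stratify the Cox model by centre, so that people are compared only within centres.

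The cost is one more model term and slightly wider 95% intervals. The change can be fixed before any follow-up data are obtained.

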### Study objectives and hypotheses

1.1.

This project was designed as a hybrid study, composed of a quantitative part (exposed in this article) and a qualitative part (published in another article).

The quantitative part of the DESVELA cohort has the following objectives:

To analyze whether personal aptitudes related to certain behaviors (self-efficacy, activation, health literacy, resilience, locus of control, and personality traits) are independently associated with the incidence of morbidity.To analyze whether personal aptitudes related to certain behaviors (self-efficacy, activation, health literacy, resilience, locus of control, and personality traits) are independently associated with lower all-cause mortality, improved engagement in healthy lifestyles, higher quality of life, and lower utilization of the health services during follow-up.

We hypothesize that personal aptitudes that are related to positive behaviors (a higher self-efficacy, activation, health literacy, resilience, an internal locus of control, and positive personality traits) will be independently associated with a lower incidence of morbidity. We also hypothesize that personal determinants related to positive behaviors (a higher self-efficacy, activation, health literacy, and resilience, an internal locus of control, and positive personality traits) will be independently associated with all-cause mortality, engagement in healthy lifestyles, higher quality of life, and more optimal use of the health services during follow-up.

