### Variables

2.4.

All the questionnaires used in the study are validated in Spanish except for the LOC, which will be assessed by a single question not yet validated. Table 1 shows the name of the questionnaire, the number of items, and the citation.

**Table 1 tab1:** Validated questionnaires used in the study.

Optional self-administration in our study	Questionnaires	Number of items	Reference of validated version in Spanish
	*Independent variables* *(Personal aptitudes)*		
Yes	Sherer’s general self-efficacy scale (GSES-12)	12	(74)
No	Patient Activation Measure (PAM)	13	(46)
Yes	10-item Connor-Davidson Scale	10	(75)
No	Health Literacy (HLS-EU-Q16)	16	(76)
No	10-Item Big Five Inventory (BFI-10)	10	(77)
	*Covariables*		
Yes	Functional social support (Duke-UNC-11)	11	(78)
Yes	WHO Disability Assessment Schedule (WHODAS 2.0)	12	(79)
Yes	List of Threatening Events (LTE)	12	(80)
Yes	Effort-Reward Imbalance questionnaire (DER/ERI)	16	(81)
	*Dependent variables*		
No	Adherence to the Mediterranean diet (Predimed and Predimed Plus)	23	(82, 83)
Yes	International Physical Activity Questionnaire (IPAQ)	4	(84)
Yes	Pittsburgh Sleep Quality Index (PSQI)	11	(85)
Yes	Quality of Life (EuroQol 5D–5 L)	5	(86)
No	Generalized anxiety disorder (GAD-7)	7	(87)
No	Depression Test Questionnaire (PHQ-9)	9	(88)
No	Depression Risk Calculator (PredictD)	2 + 12	(89)

The independent variables in this study refer to personal aptitudes, will be measured at baseline, and are listed as follows with the corresponding measurement tools: self-efficacy, which will be measured with the Sherer’s general self-efficacy scale (74); activation, measured with the Patient Activation Questionnaire (PAM) (46); resilience, measured with the abbreviated version of the 10-item Connor-Davidson scale (75); health literacy, evaluated with the HLS-EU-Q16 literacy questionnaire (76); LOC, assessed with the statement “I feel that events in my life are often determined by factors that are beyond my control” which has 6 response options in a Likert-type scale; personality characteristics will be examined using the 10-Item Big Five Inventory (BFI-10) for determination of personality traits (77).

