The evaluation of the participants’ mental health will also include the following: a questionnaire on the generalized anxiety disorder (GAD-7) (87), which evaluates the presence of symptoms; examination of the diagnostic criteria for major depression, using the PHQ-9 (88); and estimation of the risk of depression (89), in participants with no diagnosis of a major depressive episode.

We will evaluate the several lifestyles: adherence to the Mediterranean diet, assessed with the PREDIMED (82) and PREDIMED plus (83) questionnaires; type of diet, determined by asking the participants if they follow any specific diet (e.g., vegetarian, vegan); level of physical activity, assessed with the International Physical Activity Questionnaire (84); smoking habit, measured with the 4-question scale adapted from the WHO MONICA study (90); alcohol consumption, considering the total units during the past week and a question on the monthly frequency of excessive consumption (binge drinking) over the past year; and sleep, evaluated using the Pittsburgh Sleep Quality Index (85), the overall number of sleeping hours, usual bedtime, and waking-up time.

The quality of life will be determined using the EUROQol 5D-5L health questionnaire (86), and a question on self-perceived well-being. Finally, the utilization of health services for the last 12 months previous to inclusion into the study will be extracted from electronic health records. Where the research team may have no access to electronic health records, the utilization of health services will be assessed with a survey answered by the participants. The items will enquire on the number of visits (to the emergency department, primary care, and other specialties), hospital admissions, diagnostic tests, and pharmacological treatment (medication, dose, total daily dose, and duration).

Additionally, we will consider the following groups of covariates: sociodemographic, social, functional capacity, and stress level.

We will register the following sociodemographic variables: date of birth, sex, sex orientation, and gender identity (SOGI questions), marital status, nationality, and employment status. We will also consider occupational social class, defined with the educational level and occupation. Participants will answer questions on employment conditions (six items), domestic and care work (six items), income level and economic situation (four items), and housing and material situation.

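### The objective-2 follow-up models for lifestyles, quality of life and service use do not adjust for the baseline value of the outcome, so a difference already present at entry can be read as a follow-up effect

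*Protocol article*

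**What the plan says.** Objective 2 (section 1.1) asks whether the aptitudes are associated with lower mortality and with "improved engagement in healthy lifestyles, higher quality of life, and lower utilization of the health services during follow-up".

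Section 2.4 fixes the timing. Of the aptitudes it says: "The independent variables in this study refer to personal aptitudes, will be measured at baseline". Of the outcomes: "The information regarding the main dependent variables will be recorded at baseline and during the follow-ups at 5 and 10 years". For service use at entry, "the utilization of health services for the last 12 months previous to inclusion into the study will be extracted from electronic health records", with a participant survey where records cannot be reached.

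Section 2.4 also names the adjustment set: "we will consider the following groups of covariates: sociodemographic, social, functional capacity, and stress level". Table 1 lists the diet scores, IPAQ, PSQI and EuroQol under dependent variables, apart from the covariables.

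Section 2.6 analyses the incidence of the remaining dependent variables with "Cox models, one for each of the six independent variables, adjusted for the covariates". Separately, it plans multilevel models of the same lifestyle, quality-of-life and service-use outcomes on the same aptitudes at baseline, "adjusted for the registered covariates (age, sex, occupational social class, social capital, functional capacity, and stress level").

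**The concern.** Aptitude and outcome are first measured together, and the article itself plans to examine their association at that point. If people with higher health literacy already eat better or use fewer services at entry, and these traits are fairly stable, they will still differ at 5 and 10 years with nothing further having happened. A follow-up model without the baseline value cannot tell that persistence from a later change.

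This matters because section 3 presents the longitudinal follow-up as an addition to the initial cross-sectional analysis, and section 4 says the cohort meets a need for studies of behavioural change. Reverse causation is also left in the estimate: people already unwell at entry may score lower on activation or resilience. The requirement that a condition be absent at baseline is stated for the 17 morbidity groups only, and no change score is defined for the other outcomes. Objective 1 and all-cause mortality are not affected.

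**Working it through.** **Group sizes.** Section 2.3 gives 1,793 with lower and 1,290 with higher health literacy, and 30% loss. The total of 3,083 can be approximately reproduced. A two-proportion formula (0.60 against 0.66, two-sided 5%, 80% power, ratio 1,793/1,290 = 1.39, continuity correction) gives 900 in the smaller group. Then 900 × 2.39 = 2,151, and 2,151/0.7 = 3,073. The point does not depend on this figure; only the retained groups are used: 1,793 × 0.7 = 1,255 and 1,290 × 0.7 = 903.

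**Assumptions (not in the article).** The outcome is in SD units. The higher-literacy group is better by d at entry. The baseline-to-follow-up correlation is ρ. The aptitude has no effect once the baseline value is given. No part of d is absorbed by the planned covariates. The range is d = 0.1 to 0.3 and ρ = 0.4 to 0.7. Events are judged at a fixed visit with a logistic model, as a stand-in for the Cox model, because the article defines no event for these outcomes.

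**Reading A: continuous level at follow-up.** The carried-over difference is ρ × d, with SE = √(1/1,255 + 1/903) = 0.0436. The chance of p < 0.05 is Φ(z − 1.96) + Φ(−z − 1.96), with z = ρd/0.0436.
- d 0.1, ρ 0.4: z = 0.040/0.0436 = 0.92, giving 15%.
- d 0.2, ρ 0.5: z = 0.100/0.0436 = 2.29, giving 63%.
- d 0.3, ρ 0.7: z = 0.210/0.0436 = 4.81, giving over 99%.

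**Reading B: event = follow-up score above 0.5 SD, everyone analysed.** The event probability is 1 − Φ(0.5) = 0.309 in the lower group and 1 − Φ(0.5 − ρd) in the higher group.
- d 0.1, ρ 0.4: 0.323 against 0.309, odds ratio 1.07, 11% (simulations of this corner gave 9% to 13%).
- d 0.2, ρ 0.5: 0.345 against 0.309, odds ratio 1.18. The SE of the log odds ratio is √(1/(903 × 0.345 × 0.655) + 1/(1,255 × 0.309 × 0.691)) = 0.093, so z = 0.164/0.093 = 1.76, giving 42%.
- d 0.3, ρ 0.7: 0.386 against 0.309, odds ratio 1.41, 96%.

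The middle case depends on the threshold: 45% with the cut at 0 SD and 34% at 1 SD.

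**Reading C: as B, but only people below the threshold at entry.** Event-free at entry are Φ(0.5) × 1,255 = 868 and Φ(0.5 − d) × 903. Event probabilities come from the bivariate normal distribution.
- d 0.1, ρ 0.4: 0.237 against 0.232, odds ratio 1.03, 6%.
- d 0.2, ρ 0.5: 558 and 868 people, 0.223 against 0.210, odds ratio 1.08, 9%.
- d 0.3, ρ 0.7: 0.183 against 0.160, odds ratio 1.17, 19%.

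Moving the cut between 0 and 1 SD shifts the last figure to between 13% and 25%.

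**With the baseline value added.** Simulation (1,500 runs at each of the three settings) gives 4% to 6% under all three readings, against the nominal 5%.

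**The case against.** - **Incidence may already imply an at-risk set.** Section 2.6 speaks of the incidence of these outcomes and uses Cox models as in objective 1, where incidence means new onset. On that reading people already in the outcome state are excluded, and reading C applies. This is the strongest counter-argument. It shrinks the problem greatly but does not remove it, and no such state is defined for quality of life, lifestyles or service use.
- **The target may be the level, not the change.** Only the lifestyles phrase in objective 2 says improved; quality of life is to be higher and service use lower. The hypothesis in section 1.1 drops the word, section 2.1 speaks of influence, and section 3 of predictors. If the total long-run association is wanted, a persisting difference is a true finding. If aptitudes had already shaped the outcome by entry, as Figure 1's causal diagram allows, adjustment removes part of the effect. This stands, and it is why both models should be shown.
- **The article is condensed.** The covariate list in brackets in section 2.6 belongs to the baseline models, where a baseline outcome could not be a covariate, and section 2.4 does not call its list exhaustive. Even so, an adjustment set is stated, and Table 1 keeps these outcomes apart from the covariables.
- **Planned covariates absorb some of the gap.** Functional capacity (WHODAS 2.0) may take up part of a quality-of-life difference, so the figures above are upper-end for that outcome. It does not measure diet, smoking, sleep or service use.

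Two stronger readings are tempting. A reader might infer that the problem persists whatever regression is chosen. It does not: a change score, an aptitude-by-time term in a repeated-measures model, or a baseline-free risk set would remove or reduce it. A reader might also infer that the investigators intend to report persistence as improvement. No passage says so; the plan only leaves the two unseparated.

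**Conclusion.** The point holds for the secondary outcomes of lifestyles, quality of life and service use. The adjustment set as stated omits a baseline value that the study collects, and nothing else in the plan separates persistence from later change. It bears hardest on the claim about improved lifestyles.

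The size is conditional. For a 0.2 SD gap and a correlation of 0.5, the false-positive rate is 63% for a continuous level, about 42% for a thresholded event in everyone, and about 9% among people event-free at entry. The 63% should not be quoted as the figure for the planned analysis, which is worded as incidence. All three figures rest on an assumed gap and correlation, no effect beyond baseline, and no absorption by the planned covariates.

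**What to change.** In section 2.6, add to each objective-2 follow-up model, except mortality, the baseline value of the same outcome: EQ-5D-5L, diet score, IPAQ, PSQI, smoking, alcohol, or 12-month service use. Base any statement about improvement or change during follow-up on that model. Report the model without the baseline value alongside it, labelled as the total association including differences already present at entry.

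The cost is a short addition to the analysis text; no new data are needed and the sample size does not change. There are two downsides. The baseline-adjusted estimate excludes any effect of the aptitude already expressed by entry, so it may be smaller. Measurement error in the baseline value leaves some residual carry-over. Showing both models makes the first visible; the second should be stated as a limitation.
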